
### Selection of control hospitals

Structural deviations between model and potential control hospitals (similarity scores) were determined on the basis of structured quality reports according to § 137 SGB V [17] from the year 2016 (published in 2018) and matched data from the Federal Institute for Research on Building, Urban Affairs and Spatial Development (BBSR) [18], which included sociodemographic and socioeconomic data on the level of administrative districts (LANDKREISE) from the year 2016. Since the BBSR data from 2016 no longer included the number of psychotherapists and large differences in this parameter between the districts became obvious, the number of psychotherapists from the 2012 data was used instead. As the number of psychotherapists per administrative districts varied strongly over the past years, we will also examine the number of psychotherapists based on the demand planning / publication of the Association of statutory health insurance physicians [19] and include this information in the control hospital selection described above. Both lists will be compared before analyses for the interim report in Module A.

Based on these data, mandatory (i.e. hospital must have a PIA and be located in the Federal state Baden-Württemberg), hard (weighting: 50%, i.e. patients’ diagnoses) and soft criteria (25%, i.e. structural characteristics of the clinics, e.g. number of beds or personnel), and sociodemographic criteria of the region (25%, e.g. unemployment rate or average household income per inhabitant) were combined and a weighted similarity score to the model hospital was calculated.

Further details of this procedure are described elsewhere [20] and already used in other studies [21, 22]. All 16 possible control hospitals were sorted from best to least fit to the model hospital. For Module A, the ten best fitting hospitals will be selected for further consideration. The remaining possible control hospitals may be selected later in the study if chosen control hospitals merge, close or turn into a FIT model hospital. For Module B, possible control hospitals, according to the above-mentioned list, were consecutively asked to participate in the study until two control hospitals agreed to participate.

### Module A

#### Design

Module A describes the resource utilization in the model hospital including the shift from inpatient to outpatient treatment in the hospital, clinical outcomes and direct medical costs. Anonymous claims data from the SHI fund AOK Baden-Württemberg will be analyzed. Results will be separately analyzed between patients who have not been treated in the reference hospital, either model or control hospital, during the 2 years before study entry (hospital-new patients) and those who were treated at least once in the hospital in the 2 years before study entry (hospital-known patients).

All patients treated in the KJP at the UKT between January 2018 and December 2021 on an inpatient or outpatient basis, insured with the SHI fund AOK Baden-Württemberg and with follow-up data of at least 12 months after reference treatment will be included in the analysis for the IG. Due to the low number of those insured with the SHI fund SVLFG, this SHI will not be included in this analysis. The first 3 months after model project start (October – December 2017) will not be considered in this analysis due to initially incomplete implementation of model structures and benefit from consideration of complete calendar years. Patients selected via PIA treatment must be younger than 18 years of age at the time of the reference treatment.

Patients for the CG will be matched with patients from the above-described selected control hospitals. For each patient in the IG, one control patient will be matched from the patient pool of the selected control hospitals. For this purpose, two linked two-stage or mixed propensity score matches will be performed. The final decision about the consideration of patients for the analysis will be made using initial available data (power simulation).

The reference case refers to the initial treatment of the patient in either IG or CG after study onset, i.e. inclusion into the study in Module A. The reference date (Module A) refers to the date of the reference case. Outcomes in Module A will be compared to patients’ results 1 year prior to the reference case (pre-period) to better estimate the effect of FIT treatment.

#### Analysis

For each included patient, data starting from the reference date to at least 12 months and at most 48 months plus 24 months prior to reference date will be considered. Each outcome in this module, besides inpatient hospital readmission, will be compared between IG and CG and between the year prior to reference date and time after reference date (difference-in-difference approach). This approach enables the research team to observe changes in the outcomes under investigation over time and between IG and CG. The inclusion of control clinics allows the research team to mitigate the influence of unobservable exogenous effects (e.g., political or economic events) that may arise over time and affect both model and control clinics. This approach is successfully implemented in the EVA64 study [16, 21, 23].

A sample size of about 240 patients within 1 year with 120 patients in the IG and 120 patients in the CG and about 60 patient as hospital-new and 60 as hospital-known in each group is estimated. For the final report, about 600 patients are expected to be included in the dataset, i.e. 300 patients in each group, comprised of 60 hospital-new patients (4*60 patients) each year and 60 hospital-known patients. The anticipated number of patients per year is based on experiences in the IG and the relation between hospital-new and hospital-known patients on previous experiences of similar analyses [24]. An a priori power analysis for the primary outcome parameters using α = 0.05 and 1 – β = 0.80 revealed that medium effects (Cohen’s d = 0.5) could be verified with the estimated dataset.

Generalized regression models with additive modeling of the treatment effect will be used. Comparisons between IG and CG will be modeled for each measurement point (one measurement point per patient-specific year), each in relation to the pre-period. The outcome inpatient readmission is not suitable for a longitudinal analysis due to its operationalization. Therefore, the inferential statistical evaluation here will exclusively consider the first patient-specific year. Whenever possible, the models will be adjusted for confounder variables, i.e., other available influencing variables (e.g. age group, gender, comorbidity, setting of reference case) are included in the model to control for additional variance explanation of these variables.

Effects and costs will be analyzed from a SHI perspective. Primary (confirmatory) analyses will be performed according to the intention-to-treat approach firmly assigning patients to the hospital that initially filed their reference case. For the cost-effectiveness analysis, primary outcome parameters and costs will be compared between model and control hospitals using the incremental cost-effectiveness ratio as costs per one-day-of-hospital-stay avoided. A significance level of *p* ≤ 0.05 will be set for all analyses.

### Module B

#### Design

In Module B, the KJP departments of the selected control hospitals will be asked for study participation based on the above described ranked list of identified control hospitals. Recruitment of control hospitals will start with the hospital best fitting the model and continued down in ranking until at least two control hospitals will have agreed to participate. After initiation, all patients being treated in the participating hospitals within an 18-month recruitment phase starting in spring 2021 will be asked for study participation. As the targeted study population is underage, custodians, together with the patient, will be asked for informed consent regarding study participation. Custodians and siblings of the patients will also be recruited and asked for study participation and informed consent. Having given informed consent, patients, custodians and siblings will be asked by the hospital staff to complete a set of questionnaires (Table 2) (t = 0). Age-appropriate versions of the questionnaires (group of 6–7 year olds, 8–10 year olds, and 11–17 year olds) will be used for the children and adolescents. Follow-up will occur after 24 months with the same set of questionnaires used during baseline (t1).

**Table.2 Tab2:** Instruments Module B

Outcomes	Subject^a^	user^b^	ITEMS/QUESTIONNAIRES
basic data on socio-demographics	patient	patient	Age, sex, type of school, grade
		custodian	Year of onset of disease, number of former hospital stays
Disease		Staff at participating hospital	Psychiatric and somatic diagnoses (ICD-10), date of admission and discharge, setting, patient’s placement
health-related quality of life		patient	Health questionnaire KIDSCREEN-27 [25]
		custodian	Health questionnaire KIDSCREEN-27, parent version [25]
Symptom burden		patient & custodian^c^	Strengths and Difficulties Questionnaire (SDQ) [26]
Return to psychosocial relationships		patient & custodian	Own questions (friends, school, physical activity, hobbies, social integration, day structure)
treatment satisfaction		patient & custodian^c^	Treatment assessment questionnaire (FBB) [27]
costs		custodian	Own questionnaire adapted from the Client Sociodemographic Service and Receipt Inventory (CSSRI) [28] and the “Questionnaire on the use of medical and non-medical care services for mental illnesses” (FIMPsy) [29]
Burden on relatives	custodian	custodian	Questionnaire on the burden of relatives (FBA) [30]
	siblings	siblings	Health questionnaire KIDSCREEN-27 [25] for siblings Questionnaire on the burden of siblings (LARES) [31]

^a^Subject = individual about whom outcomes are measured

^b^User = individuals who fill in the questionnaire (on behalf)

^c^depends on the age of the participating patient

A nonparticipant survey will be conducted in which the reasons for nonparticipation as well as a minimum set of sociodemographic and morbidity-related data of the patients will be recorded to compare such characteristics of the study nonparticipants with those of participating patients to estimate the extent of possible selection bias. Patients asked for participation in this module must be at least 6 years old, must have sufficient cognitive and linguistic abilities to participate in the survey, and must have provided written consent (of the children and adolescents themselves plus written consent of their custodians). Patients posing an acute danger to themselves and others will not be allowed to participate in this study.

The questions on the return to psychosocial living conditions will be validated internally before use. Furthermore, a pre-test of the questionnaires (see Table 2) will be conducted. For this purpose, the questionnaires will be tested in their age-appropriate versions on at least ten children or adolescents of the respective age group (6–7, 8–10, 11–17 years) for usability (manageability & comprehension), acceptability (number of items) and faking (response tendencies). Necessary changes revealed in this pre-test will be incorporated in the final version of the questionnaires.

#### Analysis

An evaluation of the characteristics of the IG and CG, e.g. age, gender, diagnosis, etc., will be performed prior to the evaluation of the hypotheses under investigation. Patient matching via entropy balancing will be employed in this module to achieve higher power in the analysis as well as higher representativeness as a loss of subjects due to extreme covariate values is minimized with this balancing method [32–35].

It is anticipated to have about 100 patients recruited in each participating hospital, i.e. 100 in IG and 200 in CG, over the 18-month recruitment phase. Those patients will be contacted in the follow-up after 24 months. We anticipate a dropout rate of .50, based on the response rate of previously conducted studies with comparable study design. Using α = 0.05 and 1 – β = 0.80, medium effects (Cohen’s d = 0.5) could be verified within this module.

The primary outcome, health related-quality of life, will be assessed confirmatory for subgroups regarding differences between IG and CG. T-test analyses will be used to compare different groups and the analysis of covariance will be used to adjust for baseline differences and other intervening covariates. A significance level of *p* ≤ 0.05 will be set for all analyses.

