C1	Semi-structured Interviews	Families of patients being treated in the KJP of the UKT, insured with the SHI fund AOK Baden-Württemberg and treated within 18-month recruitment phase starting autumn 2021 and with social service recommendation; *n* = ca. 30	NA	Between autumn 2021 and spring 2023	Personal telephone interviews	Offer and effects of social service, benefit from social service
C2	Focus group	UKT & social service personnel	NA	Spring 2022	Focus group discussion	Cooperation between UKT and social service employees

*KJP* Department of child and adolescent psychiatry, *UKT* University Hospital Tübingen, *SHI* Statutory health insurance, *reference date* First treatment in either intervention or control hospitals between 01 January 2018 and 31 December 2021, *n* Anticipated number of study participants in each module; *NA* Not applicable

In order to ensure that potential outcome-related differences between IG and CG can be attributed solely to the intervention, both groups have to be as similar as possible to each other regarding all other aspects. Group comparability will be established in a two-step procedure. First, structurally comparable control hospitals were defined (see “selection of control hospitals” below). Second, from those identified control hospitals appropriate, comparable patients must be selected (see module descriptions). Further explanations of each module are given below. Figure 1 visualizes the study data flow in each of the modules.

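### Module B's 80% power for d = 0.5 fits a whole-group test of independent completers, not the subgroup tests called confirmatory, and the one-model-hospital confounding is not named as a limitation

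*Protocol article*

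**What the plan says.** The Module B Analysis section plans about 100 patients per participating hospital, "i.e. 100 in IG and 200 in CG, over the 18-month recruitment phase". On follow-up it says "Those patients will be contacted in the follow-up after 24 months" and "We anticipate a dropout rate of .50". The power statement follows: "Using α = 0.05 and 1 – β = 0.80", "medium effects (Cohen’s d = 0.5) could be verified within this module".

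The next paragraph describes the confirmatory assessment of the primary outcome, health-related quality of life, as being for subgroups with regard to IG–CG differences. On method it says "T-test analyses will be used to compare different groups", with analysis of covariance to adjust for baseline differences and other covariates. The 0.05 level applies to every analysis. The section gives no subgroup definition, no alpha adjustment, no hospital term and no ICC.

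The overall design section and Table 1 set the IG as the single model hospital and the Module B CG as two control hospitals. The limitations section names the small sample and the pandemic. It does not mention that the intervention is delivered in one hospital only.

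**The concern.** There are two separate problems.

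First, the power statement and the confirmatory test refer to different comparisons. The sample size supports a medium effect when all completers are compared. If the confirmatory claim is made within subgroups, each test uses only part of that sample, and the stated power does not describe it. A null subgroup result could then be read as good evidence against a medium effect when the test had roughly even odds of missing one. With several subgroups each tested at 0.05, the chance of at least one false positive also rises.

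Second, with one model hospital, hospital and intervention are the same variable. A patient-level t-test or ANCOVA treats patients as independent and counts any remaining difference between hospitals as part of the FIT effect. The article intends to judge transferability and to inform policy on standard care. For that purpose the standard error is too small whenever residual hospital variation exists, and more patients in the same three hospitals would not remove the problem.

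**Working it through.** **Inputs from the article (Module B Analysis, overall design).** α = 0.05; power 0.80; d = 0.5 (SD = 1); 100 IG and 200 CG recruits; dropout 0.50; one model and two control hospitals.

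**Assumptions, not in the article.** Two-sided testing; a two-way subgroup split; baseline correlation r; hospital ICC of 0.01, 0.02 or 0.05; 50 completers per hospital.

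**1. Reproducing the stated power.** Completers: 100 × 0.5 = 50 and 200 × 0.5 = 100. Noncentrality = d × √(n₁n₂/(n₁+n₂)) = 0.5 × √(5000/150) = 0.5 × √33.3 = 2.89, with 148 df. Power = 81.8%; detectable d at 80% power = 0.49. The smallest 1:2 sample that reaches 80% is 48 v 96, so the reserve is small. The article's figure is confirmed for this test.

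**2. Half-size subgroup, unadjusted t-test.** 25 v 50: noncentrality = 0.5 × √(1250/75) = 0.5 × √16.7 = 2.04, with 73 df. Power = 52%; detectable d at 80% power = 0.70.

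This does not depend on the split being even. The information term n₁n₂/(n₁+n₂), added over two subgroups, cannot exceed its whole-group value of 33.3. At least one subgroup therefore has 16.7 or less, and about 52% power or less. A search over two-way splits of 50 v 100 confirms that the even split is the best case for the weaker subgroup.

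Three equal subgroups give about 37% power each.

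**3. Multiplicity.** With k independent tests at 0.05, the family-wise error is 1 − 0.95^k: 9.8% for two and 14.3% for three. Halving alpha to 0.025 for two half-size subgroups lowers power at d = 0.5 to 41% and raises the detectable d to about 0.77.

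**4. Credit for the planned ANCOVA.** Adjustment for a baseline value with correlation r scales d by 1/√(1−r²). For 25 v 50:

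| r | Power at d = 0.5 |
|---|---|
| 0 | 52% |
| 0.3 | 56% |
| 0.5 | 64% |
| 0.6 | 71% |
| 0.7 | 81% |

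Only a correlation near 0.7 restores 80%, and then only with no loss from weighting or clustering.

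**5. One model hospital against two.** In SD units, the variance of the IG–CG difference is ICC × (1 + 1/2) + (1 − ICC) × (1/50 + 1/100). The patient-level test uses 0.03. True type I error = 2 × [1 − Φ(1.96 × √(0.03/variance))]. Detectable d = 2.80 × √variance.

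| Assumed ICC | Variance | Type I error of nominal 5% test | Detectable d |
|---|---|---|---|
| 0.01 | 0.015 + 0.0297 = 0.0447 | 11% | 0.59 |
| 0.02 | 0.030 + 0.0294 = 0.0594 | 16% | 0.68 |
| 0.05 | 0.075 + 0.0285 = 0.1035 | 29% | 0.90 |

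Simulating the t-test itself gave type I errors of 10.6%, 16.1% and 29.7%. The first variance term does not shrink as patients are added. The detectable d treats the ICC as known; three hospitals could not usefully estimate it.

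**The case against.** The strongest reply is that no arithmetic is wrong: 50 v 100 does give 80% power for d = 0.5. That stands. The fault lies in what the figure is attached to.

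It can also be said that the subgroup wording is ambiguous and may mean no more than IG against CG, that subgroup definitions belong in an analysis plan, and that the limitations section already concedes small effects may be missed. The ambiguity is real. But if the whole-group contrast was meant, the sentence needs correcting, and if subgroups were meant, the power statement does. A concession about small effects does not cover a shortfall for medium ones.

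On clustering, the article gives no ICC. Hospital selection by similarity score, entropy balancing and ANCOVA may remove part of the hospital variation, and inference confined to these three hospitals would not be anti-conservative. So the direction holds for an effect attributed to FIT, while its size is unknown.

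Four stronger readings are tempting but not supported:

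- That entropy balancing by itself undoes the power. The whole-group test keeps 80% down to a control effective size of 88 out of 100. At 70 it has 76%, and ANCOVA with r = 0.3 brings that back to 80%.
- That Module A is underpowered. Its statement, "revealed that medium effects (Cohen’s d = 0.5) could be verified with the estimated dataset", is missed by only 2.5 points for 60 v 60 hospital-known patients (77.5%). That is before the planned covariate adjustment, and the article foresees a power simulation on initial data.
- That the article claims attribution is already secured. The sentence opening "In order to ensure that potential outcome-related differences between IG and CG can be attributed solely to the intervention" goes on to require similar groups. It states an aim behind the selection procedure, not a result.
- That changing the matching ratio or ranking placebo hospitals would cure the design. Extra control patients do not add a second model hospital, and a ranking among one model and ten control hospitals cannot give p below 1/11 = 0.09.

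**Conclusion.** The point holds in this form. The stated 80% power is correct for one comparison, the whole-group contrast of about 50 v 100 independent completers, and does not describe subgroup tests. With any two-way split, at least one subgroup has about 52% power or less at d = 0.5 in an unadjusted two-sided t-test, and a half-size subgroup has a detectable d of about 0.70. This rests on there being at least two subgroups. ANCOVA softens it, but restores 80% only at a baseline correlation near 0.7.

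The confounding of hospital with intervention follows from the design and needs no outside figure. The inflation of type I error (11%, 16%, 29%) and the detectable effects (0.59, 0.68, 0.90) are illustrations at assumed ICCs of 0.01, 0.02 and 0.05, not estimates for this study. The missing limitation is a gap in what the article says about its own inference.

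**What to change.** In the Module B Analysis section:

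- State that 80% power for d = 0.5 applies to the whole-group IG v CG contrast of about 50 v 100 completers, assuming independent patients.
- Make that contrast the single confirmatory test in Module B and label subgroup results exploratory. If subgroups are to stay confirmatory, define them, adjust alpha and give each its own detectable effect: about 0.70 for a half-size subgroup at 0.05, and about 0.77 if alpha is halved for two.
- Report a sensitivity range for the interval and the detectable effect over a stated span of ICCs, for example 0.01 to 0.05, marked as assumed.

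In the limitations section, say that FIT is delivered in one hospital, that hospital and intervention effects cannot be separated, and that Module B compares three specific hospitals.

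In Module A, add a sensitivity analysis that sets the model hospital's estimate against the spread among the control hospitals, using a t distribution on about 9 df if ten are used. The planned analysis and the 1:1 matching can stay.

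The cost is wording plus one modest analysis of data already planned. The downside is a less favourable power statement and wider sensitivity intervals.

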The primary outcome measures for this evaluation are the change in inpatient psychiatric treatment and in quality of life. Stabilization of the family’s overall care situation will be used to sustain these improvements. Using qualitative research methods, the experiences with and the subjective benefit of the social service of the AOK Baden-Württemberg as well as the cooperation of this social service with the UKT will be examined in more detail. In addition, the costs of the FIT model care should not exceed those of the standard care or, at a maximum of the same costs, better results should be achieved with regard to the above-mentioned patient-related goals.

The EVA_TIBAS evaluation study will examine the FIT model project’s effectiveness in terms of treatment and patient-related outcomes, direct medical and indirect costs, and cost-effectiveness of the model compared to standard care.

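### Module B calls unnamed subgroup tests of its primary outcome confirmatory, Module A splits its own by stratum and year, and every test is run at 0.05 with no decisive contrast named

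*Protocol article*

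**What the plan says.** The Background names two primary outcomes: "The primary outcome measures for this evaluation are the change in inpatient psychiatric treatment and in quality of life". Module A supplies the first and Module B the second.

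**Module B, Analysis.** "The primary outcome, health related-quality of life, will be assessed confirmatory for subgroups regarding differences between IG and CG". No subgroup is listed. T-tests are planned for group comparisons and ANCOVA for adjustment, without ranking the two. The same section states "A significance level of *p* ≤ 0.05 will be set for all analyses". It also states, for alpha 0.05 and power 0.80, that "medium effects (Cohen’s d = 0.5) could be verified within this module", with 100 intervention-group (IG) and 200 control-group (CG) patients recruited and 50% dropout.

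**Module A, Design.** "Results will be separately analyzed between patients who have not been treated in the reference hospital" in the two preceding years and those who have, i.e. hospital-new and hospital-known patients.

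**Module A, Analysis.** Comparisons of IG and CG "will be modeled for each measurement point (one measurement point per patient-specific year", each relative to the pre-period. Follow-up runs from 12 to 48 months, so there are one to four yearly points. The primary analyses are labelled confirmatory where the intention-to-treat assignment is described, and again a level of "0.05 will be set for all analyses". The power statement is that "medium effects (Cohen’s d = 0.5) could be verified with the estimated dataset".

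**The concern.** A significance level of 0.05 limits the false-positive risk to 5% for one test. Here a primary outcome can reach significance by several routes: two strata, up to four years, an unstated number of subgroups, and two test types. The text shown does not say which of them settles the question.

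The article goes further than silence that an analysis plan could fill. It gives confirmatory status to undefined subgroups and fixes 0.05 for every analysis, so a later plan that adjusted alpha or demoted the subgroups would depart from published wording.

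The Conclusions say the results will inform policy makers on moving the model, or parts of it, into standard care. If only year 2 in hospital-new patients were significant, or only one Module B subgroup, or if the t-test and ANCOVA disagreed, the text gives no rule for reading the result.

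**Working it through.** **Inputs from the protocol article.** Module A: two strata, up to four yearly points, 0.05 per test; 300 per group, made up of 240 hospital-new and 60 hospital-known. Module B: 100 IG and 200 CG recruited, 50% dropout, hence 50 and 100 completers; d = 0.5, alpha 0.05, power 0.80.

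**Assumptions.** Two-sided tests (sidedness is not stated), correlations between tests, and the number of Module B subgroups.

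**1. Reproduce the Module B power.** Power = Φ(d/√(1/n₁ + 1/n₂) − 1.96).
- Whole sample, 50 vs 100: √(0.02 + 0.01) = 0.1732; 0.5/0.1732 = 2.887; Φ(0.927) = 82.3% (t-test 81.8%). The stated 80% is reproduced for one whole-sample test.
- One of two equal subgroups, 25 vs 50: √(0.04 + 0.02) = 0.2449; 0.5/0.2449 = 2.041; Φ(0.081) = 53.2% (t-test 52.2%).

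**2. Module A, chance of at least one false significant result in 2 × 4 = 8 tests.**
- Independent tests: 1 − 0.95⁸ = 33.7%.
- Yearly tests equally correlated within a stratum, strata independent (simulation, 400,000 draws):

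| Correlation between years | Either direction | False benefit only |
|---|---|---|
| 0 (exact) | 33.7% | 1 − 0.975⁸ = 18.3% |
| 0.5 | 28.6% | 14.9% |
| 0.7 | 24.3% | 12.6% |
| 0.9 | 17.9% | 9.2% |

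A single two-sided 5% test gives 5% and 2.5% respectively.

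**3. Module B, disjoint subgroups with one test each.**
- Two subgroups: 1 − 0.95² = 9.75%.
- Three subgroups: 1 − 0.95³ = 14.3%.

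If the t-test and the ANCOVA each counted, at an assumed correlation of 0.85 or 0.70, the figures would be about 7–8% with no subgroups, 14–16% with two and 21–23% with three. The second test type adds little by itself.

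**4. Cost of controlling the error.**
- One test in Module B at 0.05: power stays at about 82%.
- One test in Module B at 0.025 (critical value 2.241): Φ(2.887 − 2.241) = 74.1% (t-test 73.3%).
- Module A pooled, 300 vs 300 at d = 0.5: above 99.9% at either level.
- Module A with 0.025 per stratum: hospital-new, 240 vs 240, 99.9%; hospital-known, 60 vs 60, 69.1% (t-test 68.0%), against 78.2% at 0.05.

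The Module A power figures treat d = 0.5 as a simple two-group comparison.

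**The case against.** Several stronger readings are tempting, and the document does not support them.

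- **That Module A plans eight confirmatory tests.** A reader might infer this from strata times years. But the confirmatory label is attached to the intention-to-treat assignment, and neither the stratified nor the yearly analyses are called confirmatory. The outcome definition refers to all included patients. The eight-test figure is therefore conditional.
- **That no decisive contrast exists.** The hypotheses are set out in Fig. 2, which is not available here, and an analysis plan may name the contrast. One can say only that the text shown names none.
- **That the Module B t-test ignores the balancing weights.** Entropy balancing is planned for the module with no exemption for the t-test. What stands is that the two tests are not ranked.
- **That the subgroups are the three age bands.** Those bands serve the questionnaire versions and the pre-test. The subgroups are undefined, and the word itself is ambiguous.
- **That one study-wide error rate applies.** The article says each module has its own research questions and hypotheses, so pooling the modules would be a choice of the reader.

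The independence figure of 34% is also an upper value. Yearly contrasts share patients and a common pre-period, so some correlation is likely. The objectives are directional, which makes the false-benefit figures relevant too.

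These points limit the size of the problem but do not remove it. Confirmatory status for unnamed subgroups and 0.05 for all analyses are both explicit, and even at a yearly correlation of 0.9 the Module A figure is about 18%.

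**Conclusion.** The point holds in a conditional form. In Module B the fault is in the text itself: confirmatory testing in undefined subgroups, two unranked tests, and 0.05 throughout. In Module A the status of the stratum and yearly results is left open at the same level.

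If they all carry confirmatory weight, the risk of at least one false significant result is about 18–34% in Module A, and about 10–14% in Module B under an assumed two to three disjoint subgroups with one test each. For false claims of benefit only, the risk is roughly half. An exact figure cannot be derived, because neither the subgroups nor the correlations are given. The results do not support a single error rate for the whole study.

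The Module B power statement describes one whole-sample test. It does not cover the subgroup tests that the same section calls confirmatory.

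**What to change.** **Module B.** Make the whole-group, entropy-balanced comparison of 24-month quality of life, by ANCOVA adjusted for baseline, the single confirmatory test. Report subgroups and the t-test as exploratory.

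**Module A.** Keep the planned model and outcome, and name one confirmatory difference-in-difference contrast (IG minus CG change from the pre-period). It may be one overall contrast, or one per stratum with alpha split or tested in a fixed order. Report the remaining stratum-by-year results as exploratory. An equal split lowers power in the small hospital-known stratum to about 68–69% for d = 0.5, so an overall contrast or an ordered test may be preferable.

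**Across modules.** Treat each module as its own 5% family, since their hypotheses differ. The Module B power statement is then unchanged. If one overall claim may rest on either module, use Holm and disclose that Module B power could fall to about 73–74% when it has to be tested at 0.025.

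**Cost.** No data collection or recruitment changes. The decision must be written down before outcome data are analysed, and subgroup and yearly results can no longer be called confirmatory.
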